## Background

End-stage renal disease (ESRD) is a global public health problem characterised by a significant loss in kidney function, causing retention of metabolic waste products, salt and fluid in the body [1]. The accumulation of these waste products can become fatal unless renal replacement therapy (i.e. dialysis or kidney transplantation) is sought. It is estimated that there are more than 1.4 million people receiving renal replacement therapy worldwide [2], with the ESRD incidence rate increasing at an annual growth rate of 8 % [3].

Adults with ESRD on dialysis are at high risk for foot ulceration and subsequent lower extremity amputation [4–12]. This risk is similar to those with diabetes [5, 12, 13]. Not surprisingly, individuals who are both diabetic and dialysis-dependent have even higher rates of foot ulceration and amputation [5, 14]. Foot ulceration is a major public health concern and can have a detrimental impact on an individual’s general health, functional status and health-related quality of life [15–17]. Chronic foot ulcers progress to other serious lower extremity complications such as deep infections, and result in subsequent hospitalisation, limb loss, and foot-related mortality [5, 7, 18, 19]. In addition, the treatment and management of foot ulcers generates a considerable financial burden with increased demand on health care systems [20–22]. For example, a recent study [23] conducted in the United States reported the annual cost of diabetic foot ulceration on public and private payers is between US$9 - $13 billion, not including the costs associated with diabetes management itself.

The incidence of foot ulceration in the dialysis population is currently uncertain. However, a recent retrospective study by Lavery et al. [14] estimated a cumulative foot ulceration incidence rate of 210 per 1000 person-years in dialysis patients with coexisting diabetes. The central determinants for the development of foot ulcers in the dialysis setting are poorly understood, although meta-analyses performed in our recent systematic review found that possible risk factors include: previous foot ulceration or lower extremity amputation, peripheral arterial disease, coronary artery disease, diabetes mellitus (increasing with longer duration of disease), peripheral neuropathy, retinopathy, lower serum albumin levels and higher serum phosphorus levels [24].

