### Baseline appointment

Data will be collected at the baseline appointment via an interview with the participant and by reviewing medical records and routine blood test results. Baseline variables or factors relating to participant characteristics, comorbidities and laboratory blood test results (Table 1) were selected based on the findings of our systematic review [24] and from a comprehensive review of the diabetes literature. An average of the three latest blood test results (i.e. C-reactive protein, serum albumin, total calcium, serum phosphate, parathyroid hormone, glycated haemoglobin and haemoglobin) will be obtained at baseline for the purposes of statistical analysis.

**Table 1 Tab1:** Baseline data: participant characteristics, comorbidities and laboratory blood test results

Participants characteristics	Comorbidities	Laboratory blood test results
Age (years)	Diabetes (documented diagnosis in medical history, including type and duration)	C-reactive protein (mg/L)
Sex (male or female)	Retinopathy (documented diagnosis in medical history)	Serum albumin (g/dL)
Height (m)	Known peripheral neuropathy (documented diagnosis in medical history)	Total calcium (mmol/L)
Weight (kg)	Known peripheral arterial disease or history of lower extremity revascularisation procedure (documented diagnosis in medical history or documented lower extremity revascularisation procedure e.g. angioplasty)	Serum phosphate (mmol/L)
		Parathyroid hormone (pmol/L)
		Glycated haemoglobin (%)
		Haemoglobin (g/L)
Body mass index (kg/m^2^)	Hypertension (documented diagnosis in medical history and must be requiring medication)	
Smoking history (past, current, never)	Dyslipidaemia (documented diagnosis in medical history)	
Living arrangements (living alone)	Ischaemic heart disease (documented diagnosis of ischaemic heart disease, angina, myocardial infarction or coronary bypass surgery in medical history)	
Ethnicity		
• Indigenous Australian (Aboriginal or Torres Strait Islander)		
• English	Congestive cardiac failure (documented diagnosis in medical history)	
• European		
• American		
• African	Cerebrovascular disease (documented diagnosis of cerebrovascular accident or transient ischaemic attack in medical history)	
• Asian		
• Pacific Islander		
• Other		
Cause of end-stage renal disease		
• Diabetic nephropathy	Osteoarthritis (documented diagnosis in medical history)	
• Hypertensive nephropathy		

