### Data handling and statistical analysis

Data will be entered into a Microsoft Excel® spread sheet for the development of an analytical file. A predefined statistical analysis plan will be established between an experienced biostatistician ([name]) and the research team prior to commencing the analysis. Baseline sociodemographic, health-related quality of life and clinical characteristics of participants will be calculated and expressed as mean ± standard deviation or median (25^th^ to 75^th^ percentile) for continuous variables and number (proportion) for categorical variables. For comparison of baseline variables between different groups (for example, foot ulcer or no foot ulcer), independent samples *t*-tests will be calculated for continuous variables and chi-square (*χ*^2^) tests for categorical variables. Unadjusted foot ulcer incidence rates will be calculated for number of events per 1000 person-years. Multivariate Cox proportional hazards models will be used to assess predictors of new foot ulceration and time to event secondary outcomes. Logistic regression will be used for binary outcomes, such as prevalence of foot ulcerations.

Base regression models will be developed to fit each risk factor one at a time with other variables including baseline demographics and possible confounders as described in Table 9 [9, 76, 77], and statistical significance will be assessed. As a sensitivity analysis, we will also use forward selection when building models with *P*-values set at 0.1. Confounders will be retained if they change the estimated associations between risk factors and the outcome by 10 % or more, or are significant at the 5 % level in adjusted models [78]. After a number of iterations, all risk factors will then be combined in a multivariable regression model. Possible interactions will also be assessed. Strata specific analysis of regression models using diabetes (yes/no) and sex (male/female) will be conducted to assess variables for possible effect modification. Interaction terms will then be included in the regression models if there is evidence of an effect modification from any of these variables. Risk estimates will be presented as hazard ratios and/or odds ratios (depending on the regression model) with corresponding 95 % confidence intervals (CIs). Statistical significance will be set at the conventional level of *P* < 0.05.

**Table 9 Tab9:** Risk factors and potential confounding variables

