Continuous variables	Categorical variables
Participant characteristics	Participant characteristics
• **Age**	• **Male sex**
• **Body mass index**	• **Current smoker**
Health-related quality of life (SF-36v2®)	• **Living alone**
• Physical Component Score	Comorbidities
• Mental Component Score	• **Diabetes mellitus**
Comorbidities	• **Retinopathy**
• **Duration of diabetes**	• **Peripheral neuropathy**
Dialysis-related variables	• **Peripheral arterial disease**
• **Duration of dialysis**	• **Arterial calcification**
Laboratory blood tests	• **Hypertension**
• C-reactive protein	• **Dyslipidaemia**
• Serum albumin	• **Ischaemic heart disease**
• Total calcium	• **Congestive cardiac failure**
• Serum phosphate	• **Cerebrovascular disease**
• Parathyroid hormone	• Osteoarthritis
• Glycated haemoglobin (HbA1c)	• Inflammatory arthritis
• Haemoglobin	Lower extremity complications
Other	• **Previous foot ulceration**
• Peak plantar pressures	• **Current foot ulcer present at baseline**
	• **Previous lower extremity amputation**
	Other
	• Reduced range of motion of the 1^st^ metatarsophalangeal joint
	• **Foot deformity**
	• **Inappropriate/ill-fitting footwear**
	• Skin pathology
	• Nail pathology
	• Poor foot health care behaviours
	• Regular podiatry attendance

Potential confounding variables that will be considered in the regression models are boldface

Intra-examiner reliability of the assessor ([name]) will be evaluated using ICCs for continuous data and the weighted kappa (κ) statistic for ordinal data. To assess the strength of linear correlation between the two measurements (i.e. to detect random and systematic errors) [25], ICCs and corresponding 95 % CIs of the type (3, 1) will be calculated for single measures and type (3, *k*) for average measures. ICC values >0.75 indicate good reliability, ICCs ranging from 0.50 to 0.75 imply moderate reliability and ICCs <0.50 suggest poor reliability [25]. The 95 % Limits of Agreement will also be calculated to examine the level of agreement between the two measurements [25, 79]. Absolute agreement in addition to linear weighted kappa will be calculated for ordinal data to determine the proportion of the total amount of agreement between the two measurements that is not explained by chance [80, 81]. Weighted kappa values >0.8 represent excellent agreement, >0.6 substantial levels of agreement, 0.4 to 0.6 moderate agreement and <0.4 poor to fair agreement [25].

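### The one-at-a-time model for total calcium leaves serum albumin out of its designated covariates, so the base-model calcium hazard ratio may partly reflect albumin

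*Protocol article*

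**What the plan says.** The Baseline appointment section and Table 1 fix the laboratory data: "An average of the three latest blood test results (i.e. C-reactive protein, serum albumin, total calcium, serum phosphate, parathyroid hormone, glycated haemoglobin and haemoglobin") are taken for analysis. Total calcium is the only calcium measure. Neither an albumin-corrected nor an ionised value is described.

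The section on data handling and statistical analysis sets out the modelling in steps:

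- First step: "Base regression models will be developed to fit each risk factor one at a time with other variables including baseline demographics and possible confounders" from Table 9. Significance is assessed at this step, and the general rule is "Statistical significance will be set at the conventional level of *P* < 0.05".
- Sensitivity analysis: forward selection with an entry P-value of 0.1.
- Last step: "After a number of iterations, all risk factors will then be combined in a multivariable regression model".

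The note to Table 9 identifies the confounders: "Potential confounding variables that will be considered in the regression models are boldface". By count, 22 of the 39 listed variables are boldface. "Total calcium" and "Serum albumin" are both among the 17 that are not.

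The Background, summarising the group's own meta-analyses, includes "lower serum albumin levels and higher serum phosphorus levels" among the possible risk factors for ulceration.

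**The concern.** Part of circulating calcium is bound to albumin, so total calcium tends to fall when albumin falls, whatever the mineral status. This is general laboratory knowledge and is not stated in the protocol. If low albumin also goes with more ulcers, as the Background suggests it may, albumin is linked to both the exposure and the outcome in the calcium model. Leaving it out shifts the calcium log hazard ratio downwards. Low calcium could then look like a risk factor when it only marks low albumin, and a true association with high calcium could be masked.

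The rule that keeps a confounder when it changes the estimate by 10 % or more does not clearly rescue the base model. It applies to confounders, and albumin is not designated as one. The Discussion criticises earlier studies for inadequate control of confounding, so a gap of this kind is worth closing.

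**Working it through.** The documents give no figure for calcium or albumin, so there is nothing to reproduce. The check has two parts: which models contain albumin, and how large the effect could be where it is absent.

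**Which models contain albumin**

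- Base model for calcium: the designated covariates are demographics and the boldface variables. Albumin is not designated.
- Forward selection: albumin is present only if it is selected.
- Combined model: all risk factors enter, so calcium and albumin are both present and the calcium estimate is adjusted for albumin.

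**Size at the base-model stage**

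All inputs here are assumptions except the sample size. Let r be the calcium-albumin correlation and take hazard ratios per SD. With no true calcium effect, the omitted-variable approximation is

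log HR(calcium, without albumin) ≈ r × log HR(albumin).

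First set, r from 0.1 to 0.5 and albumin HR from 0.6 to 0.8 per SD:

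- Weak end: 0.1 × ln 0.8 = −0.022, HR 0.98.
- Middle: 0.3 × ln 0.7 = −0.107, HR 0.90.
- Strong end: 0.5 × ln 0.6 = −0.255, HR 0.78 (0.775 before rounding).

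Second set, built from a slope of 0.02 mmol/L calcium per 1 g/L albumin, where r = 0.02 × SD(albumin) / SD(calcium). Table 1 lists albumin in g/dL; the choice of unit does not alter results per SD.

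- SD(albumin) 4 g/L, SD(calcium) 0.20 mmol/L, albumin HR 0.95 per g/L: r = 0.40; 0.40 × 4 × ln 0.95 = −0.082, HR 0.92.
- SD(albumin) 5 g/L, SD(calcium) 0.15 mmol/L, albumin HR 0.90 per g/L: r = 0.67; 0.67 × 5 × ln 0.90 = −0.351, HR 0.70.

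Across both sets the spurious HR per SD of calcium runs from about 0.98 to about 0.70.

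**Chance of a false positive**

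After the planned 20 % loss, 430 × 0.8 = 344 participants remain. The Background's rate of 210 per 1000 person-years, which is for dialysis patients with diabetes, would give 344 × 0.21 = 72 events if it held for everyone. A range of 40 to 80 events was used, with standard error 1/√events. The chance of P < 0.05 for calcium under the first set runs from about 5 % (r = 0.1, albumin HR 0.8, 40 events) to 63 % (r = 0.5, albumin HR 0.6, 80 events). At r = 0.3 and albumin HR 0.7 it is 10 to 16 %.

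**Simulation of the middle case**

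Cox models were fitted with n = 344, 12 months of follow-up, r = 0.3, albumin HR 0.7, about 65 events and 400 replicates:

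| Model | Mean calcium HR per SD | Rejection rate |
|---|---|---|
| Without albumin | 0.90 | 14 % |
| With albumin | 1.00 | 6 % |

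The 6 % is compatible with the nominal 5 %, since its simulation error is √(0.0625 × 0.9375 / 400) = 0.012.

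With albumin in the model, total calcium and linearly albumin-corrected calcium gave the same calcium coefficient (largest difference below 1e-15). This is expected, because the correction only subtracts a multiple of a covariate that is already fitted.

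**The case against.** A reader might infer that calcium is never adjusted for albumin, so that its reported hazard ratio must be partly an albumin effect. The protocol does not support that. Its last modelling step combines all risk factors, and the calcium estimate from that model is adjusted for albumin. Whether so large a model would be stable is a separate question, and this point does not rest on it.

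A reader might also infer that the base model cannot contain albumin. That is too strong as well. The text speaks of other variables that include demographics and confounders, which is not an exhaustive list. The Table 9 note says which confounders will be considered and does not bar others.

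Three further objections carry weight:

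- **Size.** The correlation, the SDs and the albumin hazard ratio are not in the documents. The 0.70 end combines the least favourable values: an albumin HR of 0.90 per g/L with SD 5 g/L is about 0.59 per SD. The approximation also ignores the boldface covariates, which include previous and current ulcers, neuropathy, arterial disease and diabetes. Only the albumin association that remains after those can bias calcium.
- **Importance.** Calcium is one of 39 variables, is not among the Background's suspected risk factors, and is not a sample-size predictor. The Background calls low albumin only a possible risk factor.
- **Level of detail.** A separate analysis plan is due before analysis, and covariates for one laboratory predictor could be left to it. This objection does not remove the point, because the article does fix a confounder set in Table 9. That set omits albumin at the step where significance is assessed.

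**Conclusion.** The point holds for the one-at-a-time base models, and for the forward-selection sensitivity analysis if albumin is not selected. There, total calcium is tested without albumin as a designated covariate, and its hazard ratio may partly reflect albumin. It does not hold for the combined model.

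The size is unknown from the documents. The 0.98 to 0.70 range rests wholly on assumed inputs and on no true calcium effect, and it takes no account of the boldface covariates. At its weak end the effect is negligible. Severity is minor.

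**What to change.** In Table 9 or the analysis plan, designate serum albumin as a covariate in the total-calcium base model, and keep it in the forward-selection run whenever calcium is assessed. Albumin-corrected calcium is not needed once albumin is in the model, because the calcium coefficient is the same.

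Both analytes are already collected. The cost is one line of text and one degree of freedom in the calcium base model.

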### Study design

The design is a multi-centre prospective observational cohort study with a 12 month follow-up period. Initially, we performed a systematic synthesis of existing literature to quantify the major risk factors for foot ulceration and amputation in adults with ESRD treated with dialysis [24]. Our decision on which risk factors to include in this prospective observational cohort study is based not only on our systematic review findings [24], but is also informed by a comprehensive review of the diabetes literature. A 12-month follow-up period was chosen as it will provide an adequate time frame for the development of new foot ulceration [26, 27].

Data collection will consist of two appointments; a baseline appointment and a follow-up appointment. One examiner ([name]) will conduct the baseline and follow-up appointments on all participants. Figure 1 outlines the study design. Data to be collected at baseline will be obtained from an interview with the participant, medical record review, completion of a health-status questionnaire and a non-invasive foot assessment. A comprehensive literature review was performed to determine the most valid and reliable tools to measure suspected risk factors, for use in the foot assessment. The data collection form for the baseline data is available in Additional file 1. In addition, twenty participants will also be recruited to a reliability study to assess the repeatability of the foot assessment tools. These participants will be screened for suspected risk factors for foot ulceration on two separate occasions by the same examiner ([name]), with each assessment spaced one week apart. The foot assessments to be repeated on the twenty participants in the reliability study (i.e. one week later) includes: protective sensation with the Baily Instruments Ltd® (Salford Quays, UK) Semmes-Weinstein 5.07/10 g Monofilament, vibration perception threshold with the Horwell® (Wilford, Nottingham, UK) Neurothesiometer, toe-brachial pressure index with the SysToe® (Atys Medical, Soucieu-en-Jarrest, France) system, ankle-brachial index using the Doppler ultrasound technique and first metatarsophalangeal joint range of motion with a goniometer. One examiner ([name]) will perform all of the foot assessments on the participants, thus ensuring consistency and accuracy in the measurements, and reducing the chance of systematic error.

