There are several strengths of our study. Firstly, the baseline data collection form (Additional file 1) is based on the findings of our systematic review [24] and from a comprehensive review of the diabetes literature. Secondly, one examiner ([name]) will perform all of the foot assessments on the participants, thus ensuring consistency and accuracy in the measurements, and reducing the chance of systematic error. Thirdly, we will assess the reliability of the foot assessment tools. Twenty participants will be included in a reliability study, which will evaluate the reproducibility of the testing procedures. A one week test-retest interval was chosen as it is sufficient time to avoid fatigue, learning or memory effects, and will also avoid genuine changes in the measurement variables [25]. Fourthly, the study protocol has been pragmatically designed to encompass a full range of risk factors and to ensure that the findings can be generalised and applied to clinical practice (if there are significant risk factors for foot ulceration identified). Finally, a prospective sample size calculation was performed to ensure that the study is adequately powered.

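### The reliability ICCs are given the task of detecting systematic error, but type (3,1) and (3,k) coefficients do not respond to a constant shift between sessions

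*Protocol article*

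**What the plan says.** In the protocol article, Study design says that "twenty participants will also be recruited to a reliability study to assess the repeatability of the foot assessment tools". The same examiner makes both assessments, one week apart. For continuous measures, Data handling and statistical analysis states the purpose of the ICCs as "To assess the strength of linear correlation between the two measurements (i.e. to detect random and systematic errors". It then fixes the forms: ICCs "of the type (3, 1) will be calculated for single measures" and "type (3, *k*) for average measures". It does not define k.

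One verdict scale follows for both forms: "ICC values >0.75 indicate good reliability, ICCs ranging from 0.50 to 0.75 imply moderate reliability and ICCs <0.50 suggest poor reliability". The next sentence adds a second statistic: "The 95 % Limits of Agreement will also be calculated to examine the level of agreement between the two measurements". That statistic has no acceptance limit and no good/moderate/poor label.

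Table 2 records vibration perception threshold as the average of three readings within a visit.

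**The concern.** The purpose and the chosen coefficient do not match. A type-3 ICC, as that label is conventionally defined, asks whether participants keep their relative positions from one session to the next. It does not ask whether the two sessions give the same value. Linear correlation, which the sentence names as the target, has the same blind spot.

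What is at stake is the label given to each tool. For continuous data the ICC is the only statistic with a verdict scale, so it will decide whether a tool is described as good, moderate or poor. Agreement on the raw scale is the relevant property here, because these measurements are later cut at fixed raw values: vibration above 25 V, toe index at or below 0.6, ankle index at or below 0.9, joint motion below 65°. The Discussion lists the reliability study among the strengths and says the one-week interval avoids fatigue, learning and memory effects. Such effects could shift a session mean, and the chosen ICCs cannot check for that.

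A smaller, conditional issue concerns the averaged form. If k counts the two sessions, ICC(3,k) describes the mean of two visits, whereas each cohort participant's foot assessment is made once, at baseline.

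**Working it through.** The article gives no numerical reliability figure, so there is none to reproduce. The check concerns how the coefficients behave.

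**Inputs from the article:** n = 20 participants, 2 sessions, one examiner, labels cut at 0.75 and 0.50.

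**Assumed inputs, not in the article:** the variances and the shifts used below.

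**1. Formulas.** Let MSR, MSC and MSE be the participant, session and residual mean squares of the two-way analysis of variance, with k sessions.
- ICC(3,1) = (MSR − MSE) / (MSR + (k−1)MSE)
- ICC(3,k) = (MSR − MSE) / MSR
- Absolute-agreement single-measure ICC = (MSR − MSE) / (MSR + (k−1)MSE + k(MSC − MSE)/n)

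A constant added to every second-session value changes only MSC. MSC is absent from both type-3 forms, so they cannot move.

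**2. One simulated set of 20 pairs** (between-person SD 1, error SD 0.5), with the shift added to session 2:

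| Shift (SD) | ICC(3,1) | ICC(3,k), k=2 | Absolute agreement | Mean difference |
|---|---|---|---|---|
| 0 | 0.702 | 0.825 | 0.696 | −0.17 |
| 0.5 | 0.702 | 0.825 | 0.650 | 0.33 |
| 1 | 0.702 | 0.825 | 0.443 | 0.83 |
| 2 | 0.702 | 0.825 | 0.180 | 1.83 |

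The mean difference, on which the Limits of Agreement are centred, follows the shift exactly. Over 4000 simulated sets per shift, the average ICC(3,1) stayed between 0.78 and 0.79. The average absolute-agreement ICC fell from 0.78 with no shift to 0.30 at 2 SD.

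**3. Expected values.** With two sessions, a constant shift d adds d²/2 to the denominator of the absolute-agreement ICC.

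Between-person SD 1, error SD 0.5: ICC(3,1) = 1/1.25 = 0.80 throughout. Absolute agreement = 1/(1.25 + d²/2), which is 0.78, 0.73, 0.57 and 0.31 for d = 0.25, 0.5, 1 and 2.

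Vibration-type illustration, between-person SD 10 V, error SD 3 V: ICC(3,1) = 100/(100 + 9) = 0.917 throughout. Absolute agreement:
- d = 2 V: 100/(109 + 2) = 0.901
- d = 5 V: 100/(109 + 12.5) = 0.823
- d = 10 V: 100/(109 + 50) = 0.629

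The label leaves good when 109 + d²/2 exceeds 100/0.75 = 133.3, that is d²/2 > 24.3, or d above about 7 V. In the first set it leaves good when 1.25 + d²/2 exceeds 1/0.75 = 1.333, or d above about 0.41 SD.

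**4. The averaged form.** Spearman-Brown gives ICC(k) = k·r / (1 + (k−1)r), where r is the single-measure value. With k = 2, r = 0.50, 0.60, 0.70 and 0.80 become 0.67, 0.75, 0.82 and 0.89. A one-visit value between 0.60 and 0.75, moderate on the article's scale, would read as good. With k = 3 the crossing point is r = 0.50.

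**The case against.** The strongest reply is that the paragraph already contains the right tool. The Limits of Agreement are centred on the mean between-session difference, so a constant shift is visible there. A consistency ICC paired with Limits of Agreement is a coherent choice for one fixed examiner. This stands: a reader might infer that the plan is blind to systematic error, and the article does not support that. What remains is that detecting systematic error is expressly assigned to the ICC, and only the ICC leads to a verdict.

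Second, a reader might infer that ICC(3,k) will certainly overstate one-visit reliability. The article does not establish this. With k undefined, the averaged form may be meant for scores averaged within a visit, such as the three vibration readings, and ICC(3,1) is planned for single measures in any case. Defining k may also be left to the analysis plan, which is not shown. References to two measurements and two occasions make k = 2 sessions a plausible reading, but the point stays conditional.

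Third, a reader might infer that a session shift moves cohort participants across the cut-offs. It does not. The cut-offs rest on cited literature (Neurological, Arterial and Biomechanical assessment), cohort predictors come from the baseline visit, and no exclusion or analysis decision depends on an ICC.

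Fourth, the shifts needed to change a label may be large. Under the 10 V and 3 V assumptions, a 2 V shift lowers the coefficient only from 0.92 to 0.90, and 5 V still reads good. This is fair, and the size depends entirely on assumed variances. With the other assumed set, a shift of about 0.41 between-person SDs is enough.

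Finally, the Discussion's claim that a single examiner does the work, "thus ensuring consistency and accuracy in the measurements, and reducing the chance of systematic error", concerns who measures. It neither supports nor refutes the choice of ICC.

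**Conclusion.** The point holds in limited form. The property claimed for the ICCs is wrong: type (3,1) and (3,k) coefficients, in their conventional consistency form, are unchanged by a constant difference between sessions. The article does not say consistency or absolute agreement in words. If an absolute-agreement version was intended, the type-3 label is what needs correcting.

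The practical effect is that a tool with a systematic session difference could keep the label good while its absolute agreement is only moderate or poor. How large a shift that takes rests on variances the article does not give: about 7 V under one assumed set and about 0.41 between-person SDs under the other. The averaged-form issue applies only if k is the number of sessions.

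The reach is the 20-person reliability sub-study and how its result is described. The cohort's cut-offs, the sample size, the primary outcome and the Cox models are not affected.

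**What to change.** For each continuous tool, report the two-way absolute-agreement single-measure ICC with its 95% CI. Compute it on the per-visit score that the cohort analysis uses, for example the mean of the three vibration readings. Apply the 0.75/0.50 scale to that coefficient. Beside the Limits of Agreement, report the mean between-session difference with its CI and name it as the check for systematic error.

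Define k. If it means the two sessions, do not judge ICC(3,k) on the same scale, because it describes a two-visit average that no cohort participant has.

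A smaller alternative would correct the wording alone: keep ICC(3,1), remove systematic error from its stated purpose, and assign that task to the mean difference. The verdict scale would then still rest on a coefficient that ignores a shift, so the first option is better.

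Either change is a line or two of analysis-plan text and needs no new data. The downside of the first is that the reported ICCs may be somewhat less favourable.
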